#### 10.4.2 Serious Adverse Events requiring non-expedited reporting to BCTU

Where the safety profile is well established, the causal relationship between the intervention (or the participant’s underlying condition) and the SAE, may be known. That is, such events are protocol-defined as “expected”.

Such events should still be recorded in the participant’s medical notes and reported to BCTU on the SAE form (as per section 10.5) but it does not require expedited reporting (immediately on the site becoming aware of the event) since the assessment of expectedness for the specified events has been pre-defined. These should be reported in line with the expected timeframes for other CRFs, i.e. within 4-weeks of becoming aware of the event. These events are detailed in Table 5 below.

**Table 5:** Expected SAEs in STARFISH

| Expected events related to oral steroids                  | Expected events related to intratympanic injection      | Expected events related to both oral steroids and intratympanic injection |
|-----------------------------------------------------------|---------------------------------------------------------|---------------------------------------------------------------------------|
| Blood glucose derangement requiring hospitalisation       | Complete sensorineural hearing loss following injection | Allergic reaction requiring hospital treatment                            |
| Psychotic or affective disorder requiring hospitalisation |                                                         |                                                                           |

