|                                                      |       |                                                                                                                                                                                                                                                                                                                                                                                        |
|------------------------------------------------------|-------|----------------------------------------------------------------------------------------------------------------------------------------------------------------------------------------------------------------------------------------------------------------------------------------------------------------------------------------------------------------------------------------|
|                                                      |       | 
 
• Or is otherwise considered medically significant by the Investigator**
 
                                                                                                                                                                                                                                                             |
| Serious Adverse Reaction                      | SAR   | An Adverse Reaction which also meets the definition of an SAE                                                                                                                                                                                                                                                                                                                          |
| Unexpected Adverse Reaction                   | UAR   | 
An AR, the nature or severity of which is not consistent with the applicable product information (e.g. Investigator Brochure (IB) for an unapproved IMP or (compendium of) Summary of Product Characteristics (SPC) for a licensed product).
 
When the outcome of an AR is not consistent with the applicable product information the AR should be considered unexpected.
 |

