#### 10.5.2 Assessment of expectedness of an SAE by the CI

The CI or delegate will assess all SARs for expectedness with reference to the criteria in Table 7.

If the event is unexpected, it will be classified as a Suspected Unexpected Serious Adverse Reaction (SUSAR).

The CI will review all SAEs submitted and may request further information from the site research team for any given event to assist in this review.

**Table 7:** Definition of Expectedness

| Category          | Definition                                                                                                                                                                                                                                                         |
|-------------------|--------------------------------------------------------------------------------------------------------------------------------------------------------------------------------------------------------------------------------------------------------------------|
| Expected   | An adverse event that is consistent with known information about the trial related procedures or that is clearly defined in the reference safety information:

Summary of product characteristics (SmPC) for oral prednisolone

SmPC for dexamethasone |
| Unexpected | An adverse event that is not consistent with known information about the trial related procedures or that is not clearly defined in the reference safety information.                                                                                |

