### 10.6.2 MHRA, REC and RGT

BCTU will report details of all SARs (including SUSARs) to the Medicines and Healthcare Products Regulatory Agency (MHRA), Research Ethics Committee (REC) and UoB Research Governance Team (RGT) annually from the date of the Clinical Trial Authorisation, in the form of a Development Safety Update Report (DSUR).

In addition, BCTU will report a minimal data set of all individual events categorised as a fatal or life threatening SUSAR to the MHRA, REC and RGT within 7 days of being notified. Follow-up information will be provided within an additional 8 days.

All other events categorised as non-life threatening/non-fatal SUSARs will be reported within 15 days of being notified.

The MHRA, REC and RGT will be notified immediately if a significant safety issue is identified during the course of the trial.

Details of all SUSARs and any other safety issues which arise during the course of the trial will be reported to PIs. A copy of any such correspondence should be filed in the ISF and Trial Master File (TMF).

---

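### Section 10.4.2 sorts listed serious adverse events by name alone, so a life-threatening one may take 4 weeks to reach the trials unit, on a ground that conflicts with Table 4 and section 10.5.2

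*Protocol*

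**What the plan says.** Protocol section 10.4 gives the site three routes for a serious adverse event (SAE): note it only, report it to BCTU without urgency, or report it within 24 hours. Section 10.4.2 assigns the Table 5 events to the second route. For these, "it does not require expedited reporting (immediately on the site becoming aware of the event"). The ground offered for the slower route comes in the same sentence: "since the assessment of expectedness for the specified events has been pre-defined". The time allowed is fixed there too: "These should be reported in line with the expected timeframes for other CRFs, i.e. within 4-weeks of becoming aware of the event".

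Table 5 has four entries. Two are "Allergic reaction requiring hospital treatment" and "Blood glucose derangement requiring hospitalisation". The others are psychiatric illness leading to admission and total hearing loss after an injection. Section 10.4.3 keeps the 24-hour rule for SAEs that neither 10.4.1 nor 10.4.2 lists, so being on the list is what removes an event from it.

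Three other places bear on this:

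- Section 10.1, Table 4, makes an adverse reaction unexpected if its nature or severity does not match the product information, and adds: "When the outcome of an AR is not consistent with the applicable product information the AR should be considered unexpected".
- Section 10.5.2: "The CI or delegate will assess all SARs for expectedness with reference to the criteria in Table 7". Table 7 refers to known information about the trial procedures and to the two product characteristics documents (SmPCs). It makes no exception for Table 5.
- Section 10.6.2 commits BCTU to report a "fatal or life threatening SUSAR to the MHRA, REC and RGT within 7 days of being notified".

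**The concern.** The slow route depends on the name of the event and not on how bad it was. Three of the four Table 5 entries set a floor (admission or hospital treatment), and none sets a ceiling. The gravest forms of the named harms can therefore travel by the slowest path, on the ground that the expectedness question is already answered. Under Table 4 that question cannot be answered from the name, because severity and outcome decide it.

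What is at stake is time. The chief investigator reviews SAEs once they are submitted, and BCTU can escalate only what it knows about. Until the site reports, participants continue to be randomised and treated without central knowledge of a life-threatening reaction.

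**Working it through.** This is a comparison of rules plus addition of the stated windows. The protocol gives no total of its own to reproduce.

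**Step 1. Does a life-threatening case fit the list?** Table 4 makes death and threat to life seriousness criteria in their own right, separate from hospitalisation. Sections 10.4 and 10.4.2 and Table 5 use neither to exclude a case. A life-threatening allergic reaction treated in hospital matches the Table 5 entry as worded, so section 10.4.3 does not apply and the 4-week window does.

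**Step 2. Does a fatal case fit?** Table 5 does not mention death. One site could file a fatal reaction under the listed name; another could treat death as unlisted and report within 24 hours. The text supports either reading.

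**Step 3. Is the stated ground consistent with the rest of section 10?**

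- 10.4.2 against Table 4: expectedness fixed by name, against expectedness that turns on nature, severity and outcome. They diverge for any listed event that goes beyond the product information.
- 10.4.2 against 10.5.2: expectedness fixed in advance, against assessment of every serious adverse reaction with no Table 5 exemption.
- 10.4.2 also moves from a known causal relationship straight to calling the event expected. Causality and expectedness are separate judgements in 10.5.1 and 10.5.2.

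**Step 4. Does another section close the gap?** The note in 10.4 requires the hospital's own trial team to learn of SAEs quickly; that is awareness at the site and does not shorten the window to BCTU. Section 10.5 refers back to the 10.4.2 timeline. The data monitoring committee may look at SAEs at its meetings, which section 17.5 sets at least annually. None shortens the 4 weeks.

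**Step 5. Longest compliant time from site awareness to regulator, if the event proves to be a SUSAR.** Inputs: 4 weeks = 28 days (10.4.2); 24 hours = 1 day (10.4.3); 7 days for fatal or life-threatening SUSARs and 15 days for others, both counted from notification (10.6.2). Total = site window + regulatory window.

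- Fatal or life-threatening, Table 5 route: 28 + 7 = 35 days
- Fatal or life-threatening, 24-hour route: 1 + 7 = 8 days
- Other SUSAR, Table 5 route: 28 + 15 = 43 days
- Other SUSAR, 24-hour route: 1 + 15 = 16 days

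The difference is 28 − 1 = 27 days in both cases.

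**The case against.** The best defence is that the interventions are in standard use, section 3.3 rates the trial as no riskier than usual care, and Table 5 may simply list events that already meet the Table 7 test. Most listed events would then be expected on any assessment, and targeted reporting is reasonable. That stands for the ordinary run of cases. It does not cover a listed event more severe than the product information describes, which is the case Table 4 singles out.

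Three stronger readings are tempting, and the documents do not support them:

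- **That 10.4.2 contradicts the 7-day duty.** The duty runs from notification. A site reporting on day 28 and BCTU reporting on day 35 comply with both sections. The clock starts late; it is not broken.
- **That a SUSAR could go unclassified.** Table 5 events still go to BCTU on the SAE form, causality is independently reviewed under 10.5.1, and 10.5.2 has the chief investigator review every submitted SAE. What is lost is time, not the assessment.
- **That the protocol permits sites to hold back deaths.** Table 5 is silent on death, and Table 9 schedules a trial exit form at the point the site learns of one, although section 11.2 allows four weeks for forms in general. This is an ambiguity, not a permission.

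It is also fair to say that 28 days is the maximum, not the typical delay, and that whether any given case is unexpected depends on SmPCs that are not in the protocol.

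**Conclusion.** The point holds as an internal conflict with a safety cost. As worded, a life-threatening listed reaction may wait up to 4 weeks before BCTU hears of it, the fatal case is left unclear, and the reason given cannot be squared with Table 4 or section 10.5.2. The size is an upper bound: 35 days against 8 from site awareness to regulator, 27 days longer. It assumes that each party uses its full window and that the event is judged a SUSAR. The gap at BCTU itself, up to 28 days against 1, needs no assumption about SUSAR status. Because a stated rule produces the delay and the remedy is cheap, the sponsor should correct it.

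**What to change.** - In sections 10.4 and 10.4.2 and in Table 5, state that the 4-week route applies only to listed events that are neither fatal nor life-threatening, and that every fatal or life-threatening SAE goes by the 24-hour route in 10.4.3. These are Table 4 seriousness criteria that sites already apply, so no site has to judge severity against the SmPCs before reporting.
- Replace the wording in 10.4.2 on expectedness being settled in advance with a statement that the chief investigator or delegate assesses every serious adverse reaction, Table 5 events included, under 10.5.2.

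The cost is a wording amendment, matching guidance on the SAE form and a few more 24-hour reports. No new data are needed.

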#### 10.4.3 Serious Adverse Events requiring expedited reporting to BCTU

All SAEs not listed in sections 10.4.1 and 10.4.2 must be reported to BCTU on a trial specific SAE form, within 24 hours of the site research team becoming aware of the event.

### 10.5 SAE Reporting Process

On becoming aware that a participant has experienced an SAE which requires reporting on an SAE form, the PI or delegate should report SAE to their own Trust in accordance with local practice and to BCTU.

To report an SAE to BCTU, the PI or delegate must complete, date and sign an SAE form via the STARFISH trial system using the information below in the timeline specified in sections 10.4.2 and 10.4.3. Any other relevant anonymised documents should be submitted to BCTU via the STARFISH trial mailbox ([contact]).

---

**The PI or delegate should also email [[contact]](mailto:[contact]) to make BCTU aware that an SAE has been submitted, along with any other relevant anonymised documentation.**

Where an SAE Form has been completed by someone other than the PI (or medically qualified delegate) initially, the original SAE form will be required to be countersigned by the PI (or medically qualified delegate) to confirm agreement with the causality and severity assessments.

On submission of an SAE form, a unique reference number will be assigned. The site and BCTU should ensure that the SAE reference number is quoted on all correspondence. Site should also email the trial mailbox to inform BCTU that they have submitted an SAE. If the site has not received confirmation of receipt of the SAE within 1 working day of reporting, the site should contact BCTU.

Copies of the completed SAE form should be printed on resolution of the SAE and filed in the ISF.

#### **10.5.1 Assessment of causality of an SAE**

When completing the SAE form, the PI (or, throughout this section, a medically qualified delegate) will be asked to define the nature of the severity and causality (severity; see Table 4, relatedness; see Table 6) of the event.

In defining the causality, the PI must consider if any concomitant events or medications may have contributed to the event and, where this is so, these should be reported on the SAE form. It is not necessary to report concomitant events or medications which did not contribute to the event.

**Table 6:** Definition and category of causality for AEs

| Category    | Definition                                                                                                                                                                                                             | Causality |
|-------------|------------------------------------------------------------------------------------------------------------------------------------------------------------------------------------------------------------------------|-----------|
| Definitely  | There is clear evidence to suggest a causal relationship, and other possible contributing factors can be ruled out                                                                                                     | Related   |
| Probably    | There is evidence to suggest a causal relationship, and the influence of other factors is unlikely                                                                                                                     |           |
| Possibly    | There is some evidence to suggest a causal relationship, however, the influence of other factors may have contributed to the event (e.g. the participant's clinical condition, other concomitant events or medication) |           |
| Unlikely    | There is little evidence to suggest there is a causal relationship; there is another reasonable explanation for the event (e.g. the participant's clinical condition, other concomitant events or medication)          | Unrelated |
| Not related | There is no evidence of any causal relationship                                                                                                                                                                        |           |

On receipt of an SAE form, BCTU will facilitate an independent review of causality of the SAE by the Chief Investigator (CI) or delegate. Where the CI is also the reporting PI an independent clinical causality review will be performed.

As per Table 6, all events considered to be 'possibly', 'probably', or 'definitely' related to the intervention will be reported by the trial office as 'related'; all events considered at site to be 'unlikely' or 'unrelated' to the intervention will be reported by the trials office as 'unrelated'. The same categorisation should be used when describing AEs and protocol-exempt SAEs in the source data.

An SAE judged by the PI or CI "or delegate(s)" to have a reasonable causal relationship ("Related" as per Table 6) with the intervention will be regarded as a related SAE (i.e., SAR).

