|                              | Severe   | Incapacity with inability to do work or perform usual activities.                                                                                                                                                                                                                                                                                                                                                                                                                                     |
| Adverse Event         | AE       | 
Any untoward medical occurrence in a participant or clinical trial subject administered a medicinal product and which does not necessarily have a causal relationship with this treatment.
 
Comment:
 
An AE can therefore be any unfavourable and unintended sign (including abnormal laboratory findings), symptom or disease temporally associated with the use of an investigational medicinal product, whether or not related to the investigational medicinal product.
 |
| Adverse Reaction      | AR       | 
All untoward and unintended responses to an IMP related to any dose administered.
 
Comment:
 
An AE judged by either the reporting Investigator or Sponsor as having causal relationship to the IMP qualifies as an AR. The expression reasonable causal relationship means to convey in general that there is evidence or argument to suggest a causal relationship.
                                                                                                        |
| Serious Adverse Event | SAE      | 
Any untoward medical occurrence or effect that:
 

● Results in death

● Is life-threatening*

● Requires hospitalisation or prolongation of existing hospitalisation

● Results in persistent or significant disability or incapacity

● Is a congenital anomaly/birth defect

                                                                                                                                        |

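### Section 10.5.1 contradicts itself on how the trial office reports an SAE that the site judges unrelated but the Chief Investigator judges related

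*Protocol*

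**What the plan says.** The rules are in section 10 of the protocol, most of them in 10.5.1.

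- **Central review.** When an SAE form arrives, "BCTU will facilitate an independent review of causality of the SAE by the Chief Investigator (CI) or delegate". If the CI is also the reporting Principal Investigator (PI), someone independent does the review.
- **Trial office label.** One sentence reduces the five categories of Table 6 to two labels. Its first half says that "all events considered to be 'possibly', 'probably', or 'definitely' related to the intervention will be reported by the trial office as 'related". Its second half says that "all events considered at site to be 'unlikely' or 'unrelated' to the intervention will be reported by the trials office as 'unrelated".
- **SAR rule.** The next paragraph says that an SAE judged to have a reasonable causal relationship by the PI or the CI, or their delegates, "will be regarded as a related SAE (i.e., SAR").
- **Definition in Table 4 (section 10.1).** "An AE judged by either the reporting Investigator or Sponsor as having causal relationship to the IMP qualifies as an AR".
- **What follows from SAR status.** Under 10.5.2, "The CI or delegate will assess all SARs for expectedness with reference to the criteria in Table 7", and an unexpected SAR is classified as a SUSAR. Under 10.6.2 the coordinating unit (BCTU) reports all SARs annually, fatal or life-threatening SUSARs within 7 days and other SUSARs within 15 days.

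**The concern.** The first half of the labelling sentence does not say whose judgement counts. The second half ties the unrelated label to the site's judgement and makes no exception for a CI who disagrees. Two paragraphs later in the same section, the CI's judgement alone is enough to make the event a SAR. The protocol does not say which rule takes precedence.

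This matters for one kind of disagreement: the site sees no relation and the CI does. That is the only situation in which the independent causality review adds a related event. The body given the labelling instruction is also the body that reports SARs and SUSARs to the regulator, the ethics committee and the sponsor's governance team. An instruction that gives the wrong label in that situation should not stand, even though neighbouring text gives the right answer.

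**Working it through.** The protocol states no figure on this point, so there is none to reproduce. The check sets the rules side by side for every combination of site and CI judgement. Here, related means possibly, probably or definitely; unrelated means unlikely or not related (Table 6).

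| Site | CI | Label, first half of sentence | Label, second half of sentence | SAR rule (10.5.1, next paragraph) | Consistent? |
|---|---|---|---|---|---|
| related | related | related | does not apply | SAR | yes |
| related | unrelated | related | does not apply | SAR | yes |
| unrelated | unrelated | does not apply | unrelated | not a SAR | yes |
| unrelated | related | related | unrelated | SAR | **no** |

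Three of the four combinations are consistent and one is not. In the inconsistent row, the two halves of a single sentence give opposite labels, and the second half also disagrees with the SAR rule. Table 4 supports the SAR rule in principle, since a judgement by either the investigator or the sponsor is sufficient there.

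Now follow that row through the rest of section 10, with the site saying unlikely and the CI saying possibly.

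1. The SAE form is submitted, and the CI reviews it: 10.5.2 says the CI reviews all submitted SAEs, not only those the site thinks are related.
2. Under the SAR rule the event is a SAR, because one assessor is enough.
3. Under 10.5.2 it is assessed for expectedness, and if unexpected it is a SUSAR.
4. Under 10.6.2 it goes into the annual report and, if a SUSAR, is also reported within 7 or 15 days.
5. Under the site clause, the trial office reports the same event as unrelated.

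Steps 1 to 4 depend on SAR status and not on the trial office label. The protocol therefore contains a complete route for the CI's upgrade, and step 5 contradicts it. An event drops out of that route only if staff treat the label in step 5 as settling causality.

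The number of events affected cannot be derived. The protocol gives neither an expected SAE rate nor a rate at which the CI disagrees with sites, so any count would rest on two invented inputs.

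**The case against.** The strongest defence reads the sentence in context. It opens by referring to Table 6, and the sentence after it extends the same categorisation to other events in the source data. On that reading its job is to collapse five categories into two labels, and the following paragraph decides between assessors. A CI rating of possibly already satisfies the first half of the sentence. Every later step depends on SAR status, which either assessor can confer. A missed SUSAR would need staff to apply one clause and ignore the paragraph directly below it.

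Most of this stands, and it limits the point. A reader might infer that the site clause cancels the CI's upgrade, or stops a SUSAR from being recognised. The documents do not support that: nothing gives the clause precedence, the next paragraph expressly preserves the upgrade, and 10.5.2 and 10.6.2 are keyed to SAR status. Nor is this the only contribution the CI makes, since the CI also assesses expectedness and may ask the site for more information.

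The defence does not remove the contradiction. If the sentence only collapsed categories, it would not need to name an assessor, yet it names the site in one half and nobody in the other. Read as written, it gives an instruction that conflicts with its own first half and with the SAR rule.

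**Conclusion.** The point holds as an internal inconsistency in safety reporting. For an SAE judged unlikely or unrelated at site and related by the CI, section 10.5.1 tells the trial office to report the event as unrelated and also treats it as a related event and a SAR. The contradiction is confined to one of four combinations of judgement. The likely harm is a mislabelled event; the possible harm is one left out of SAR or SUSAR reporting, and that happens only if staff follow the site clause in preference to the SAR rule.

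This conclusion rests on the wording alone and needs no assumption about event rates. It does not depend on the statistical analysis plan, because the causality and reporting rules are fixed in the protocol. It has no bearing on sample size, alpha or power. The correction is worth making because the wrong label falls where central causality review makes a difference, and because the protocol already contains the rule that resolves it.

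**What to change.** Reword the labelling sentence in 10.5.1 so that it follows the either-assessor rule already stated in the next paragraph and in Table 4. An SAE is reported as unrelated only when both the PI (or delegate) and the CI (or delegate, or the independent reviewer where the CI is the reporting PI) judge it unlikely or not related. In every other case it is reported as related.

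The cost is one sentence in the protocol, with any trial office working instruction brought into line. No new review, form or data item is needed, because the CI already reviews every submitted SAE.
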